### Inclusion and exclusion criteria

Inclusion: Children under 18 years old with suspected community pneumonia who require admission to the PICU or patients with suspected nosocomial pneumonia during their PICU stay.

Exclusion: Patients with underlying pathologies such as cystic fibrosis or who are immunocompromised. Patients who develop nosocomial pneumonia after being included in the study due to community pneumonia. Patients who have a CXR taken before being admitted to the PICU.

Withdrawal and abandonment criteria: Violation of study protocol, withdrawal of parental consent, death.

Patients withdrawing or with loss of protocol adherence will be excluded from the study.

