### Methodology

The first thing to do will be to obtain consent from the parent(s) or legal guardian(s).

Patients who meet the inclusion criteria and sign the inform consent were randomly assigned to two groups using the “random” function in MS-Excel XP® program. A binary series of random numbers were generated according to the procedure described by Friedman. To procure a similar number of patients in both groups, the procedure created the sequence through a balanced block sampling. The series of numbers were held by the principal investigator and depending on the number of the patient tit was be assigned to on or another group. A total of 8 physicians enrolled participants, and the principal investigator assigned participants to interventions, depending on the randomized list. (Fig. 1)
Experimental Group 1: The paediatrician-researcher (PR) performs the LUS at admission/suspicion as the first lung image test. If the paediatrician assistant (PA) requires a CXR, it can be performed, but the PR will not see the CXR. Patients will be subdivided into 3 groups:
If PCT is < 1 ng/mL and LUS is not suggestive of bacterial pneumonia (normal or viral), the patient will not receive an antibiotic.If LUS is suggestive of bacterial pneumonia, regardless of PCT value, an antibiotic will be recommended.If LUS is not suggestive of bacterial pneumonia, but PCT values are > 1 ng/mL, an antibiotic will be recommended to cover other infectious etiologies.Control Group 2: CXR will be performed as a first lung image test. Criteria to start an antibiotic will depend on the current unit protocol.
If PCT is < 1 ng/mL and CXR is not suggestive of bacterial pneumonia (normal or viral), the patient will not receive an antibiotic.If CXR is suggestive of bacterial pneumonia, regardless of PCT value, an antibiotic will be recommended.If CXR is not suggestive of bacterial pneumonia, but PCT value is > 1 ng/mL, an antibiotic will be recommended to cover other infectious etiologies.

Radiological and ultrasound patterns will be classified as: pneumonia (viral or bacterial), atelectasis, or parapneumonic pleural effusion (Table 2).

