LUS will be performed every day following admission and recorded and stored. LUS images will be later analysed by a paediatric radiologist who is an expert in LUS and who has not seen the initial assessment and CXR, in order to evaluate interobserver agreement. CXR will be also be reported on by a paediatric radiologist consultant who has not seen the other results.

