### Outcomes

The antibiotics protocol guided by LUS and PCT will be considered an improvement in the quality of care if a reduction in the prescription of antibiotics is observed, and also if there is a reduction in the number of days on antibiotics. Another primary outcome will be the increase in the sensitivity and specificity when diagnosing bacterial pneumonia using LUS. Secondary outcomes will be the reduction of the irradiation dose using the new protocol (with a reduction in economic costs as well), and a high LUS interobserver agreement.

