### Statistical analysis

Using the “Random” function of the MS-Excel XP® program, a binary series of random numbers will be generated, according to the procedure described by Friedman [34]. This procedure creates the sequence by means of balanced block sampling to ensure a similar number of patients in each group. The series of numbers will be in the possession of the PICU’s head researcher. Depending on that number, each patient will be assigned to one group or the other. If a patient is randomized but does not complete the treatment, their data will not be analysed, and their random number will not be reused.

The categorical variables will be compared using the Chi-square test. The quantitative analysis will be compared using Student’s t-test or the Mann-Whitney U test, depending on whether the sample follows a normal distribution or not. A multivariate logistic regression analysis will be performed on those variables with statistical significance or a clear tendency in the univariate analysis to detect which factors represent a protective factor or not, in terms of quality. The analysis of the interobserver agreement will be performed using Cronbach’s alpha. A *p* < 0.05 will be considered significant. The statistical program SPPS® 20.0 will be used.

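### Excluding randomised children for non-adherence makes membership of the analysis depend on antibiotic use, which is itself a primary outcome; an off-algorithm antibiotic after the optional CXR is one concrete route

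*Protocol article*

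**What the plan says.** All references are to the protocol article.

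- **Inclusion and exclusion criteria.** "Withdrawal and abandonment criteria: Violation of study protocol, withdrawal of parental consent, death". The section then adds: "Patients withdrawing or with loss of protocol adherence will be excluded from the study".
- **Methodology, experimental arm.** The researcher's LUS is the first image, but a film remains available: "If the paediatrician assistant (PA) requires a CXR, it can be performed, but the PR will not see the CXR". One branch of the algorithm is a flat prohibition: "If PCT is < 1 ng/mL and LUS is not suggestive of bacterial pneumonia (normal or viral), the patient will not receive an antibiotic". In the other two branches an antibiotic is only recommended.
- **Methodology, control arm.** "Criteria to start an antibiotic will depend on the current unit protocol". The three branches that follow have the same structure, with CXR as the image. The section also says "LUS will be performed every day following admission and recorded and stored", without limiting this to one arm.
- **Outcomes.** The algorithm counts as an improvement "if a reduction in the prescription of antibiotics is observed, and also if there is a reduction in the number of days on antibiotics".

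No sentence in the article keeps non-adherent children in the analysis as randomised.

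**The concern.** Adherence in this trial is largely a matter of who gets an antibiotic, and antibiotic use is also the endpoint. A rule that drops non-adherent children after randomisation therefore selects on the outcome.

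The optional film shows how. The article withholds it from the researcher, and from the radiologist who later re-reads the LUS, but not from the clinician who asked for it. Suppose the film looks bacterial while LUS does not and PCT is low. If an antibiotic is then given, the prohibition is broken and the exclusion rule applies on its plain reading. The child removed is a treated child in the experimental arm. The comparison then shows a larger reduction than the one delivered, on a criterion by which the trial will be judged.

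**Working it through.** **The plan's own figure.** The Sample size section gives 63 per arm for community pneumonia (two-sided chi-square, 5%, 80% power) but not the two proportions, so 63 cannot be reproduced from stated inputs. Several pairs come close; 0.30 v 0.10, for example, gives 62. Here 63 serves only as a denominator.

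**Step 1: direction, without accuracy assumptions.** With t treated among n children, removing one treated child gives (t−1)/(n−1), which is below t/n whenever t < n. Assume 50 of 63 treated in each arm (79.4%), so no true difference. Removing 3, 6 or 9 treated experimental children leaves 47/60 = 78.3%, 44/57 = 77.2% or 41/54 = 75.9%. The spurious reduction is 1.0, 2.2 or 3.4 points. In a simulation with 80% treated in both arms, removing 5%, 10% or 15% of the experimental arm this way raised two-sided rejection from 4.5% to 5.4%, 6.3% and 7.8%.

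**Step 2: size under an illustration.** The article gives no accuracy, CXR frequency or override rate. Assumed: 35% bacterial; LUS sensitivity and specificity 0.90; CXR sensitivity 0.80 and specificity 0.40 or 0.60; PCT above 1 ng/mL in 80% of bacterial and 10% or 25% of other children; errors independent given true status. Define

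- L = P(LUS or PCT positive), C = P(CXR or PCT positive)
- D = P(LUS negative, PCT low, CXR positive if taken)
- E = P(LUS positive, PCT low, CXR negative), N = P(all three negative)
- f = fraction of the D children who get an antibiotic against the algorithm.

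Reduction received = C − L − fD. Reduction reported after exclusion = C − L/(1 − fD). Since 1 − L = N + D, the exaggeration is fD[N + D(1 − f)]/(1 − fD).

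Example (CXR specificity 0.60, PCT positive in 25% of other children):

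- L = 1 − (0.35×0.10×0.20 + 0.65×0.90×0.75) = 0.554
- C = 1 − (0.35×0.20×0.20 + 0.65×0.60×0.75) = 0.694
- D = 0.35×0.10×0.80×0.20 + 0.65×0.90×0.40×0.75 = 0.181
- N = 0.35×0.10×0.20×0.20 + 0.65×0.90×0.60×0.75 = 0.265

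At f = 0.10, fD = 0.0181 and the exaggeration is 0.0181 × (0.265 + 0.163)/0.982 = 0.008, or 0.8 points.

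| CXR spec. / PCT+ in others | f = 0.10: received → reported (excess) | f = 0.25: received → reported (excess) | Removed of 63 (63fD) at f = 0.10; 0.25 |
|---|---|---|---|
| 0.40 / 10% | 25.3 → 27.0 (1.7) | 20.5 → 24.5 (4.0) | 2.0; 5.1 |
| 0.40 / 25% | 21.0 → 22.1 (1.2) | 17.0 → 19.7 (2.7) | 1.7; 4.2 |
| 0.60 / 10% | 14.7 → 15.8 (1.1) | 11.4 → 14.2 (2.7) | 1.4; 3.4 |
| 0.60 / 25% | 12.1 → 12.9 (0.8) | 9.4 → 11.3 (1.9) | 1.1; 2.9 |

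Over a wider grid of 1,458 settings (prevalence 25-45%; LUS sensitivity and specificity 0.80-0.95; CXR sensitivity 0.70-0.90, specificity 0.40-0.60; PCT positive in 70-90% of bacterial and 10-25% of other children) the excess is 0.4-2.6 points at f = 0.10 and 1.0-6.2 at f = 0.25. Independence of errors was not varied. With equal courses of an assumed 7 days, 1.9-4.0 points is 0.13-0.28 antibiotic days per child.

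**Step 3: what can offset it.**

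- *Untreated deviations.* Suppose 5% of experimental children with a recommendation are left untreated and also removed. The treated proportion is 0.95L + fD with all kept and 0.95L/(1 − fD − 0.05L) after exclusion. At f = 0.10 the net excess in the four rows becomes +0.6, −0.4, +0.1 and −0.7 points, so it reverses in two.
- *Control overrides.* If a fraction g of the E children in control is treated against the rule and removed, subtract gE[N + E(1 − g)]/(1 − gE). With g = f, the net excess stays positive: 0.7-1.6 points at f = 0.10 and 1.6-3.7 at f = 0.25. With f = 0.10 and g = 0.50 in the 0.60 / 10% row (E = 0.048) it falls from 1.1 to 0.3. With CXR specificity 0.80 and otherwise the same inputs it is −0.8.

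**The case against.** Allowing a clinically needed film is reasonable and is not the fault; the exclusion rule is. The route through the film is also partly inferred. The article does not say who prescribes, how often a film will be requested, or in so many words that an off-algorithm antibiotic is a violation. That last step is nevertheless the plain reading of a flat prohibition.

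A reader might infer that exclusion always inflates the reduction. The documents do not support that. Loss of adherence is wider than breaking the prohibition and can cover a child left untreated against a recommendation. The same exclusion and the same prohibition apply in the control arm. Step 3 shows that either can cancel or reverse the net effect.

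A reader might also infer a false success, with a reduction reported when none was delivered. In the illustration the received difference reaches zero only at f of about 0.77-0.89. A film would then be needed in at least 77% of the D children, with nearly every positive one overriding the rule. Nothing in the article suggests that, and it fits poorly with the aim of replacing CXR by LUS.

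Finally, the Statistical analysis section says: "If a patient is randomized but does not complete the treatment, their data will not be analysed". That is another exclusion after randomisation, but it does not naturally describe a child in the no-antibiotic branch who receives one, so it adds little here.

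What remains does not depend on the override rate: the article prescribes an exclusion that can be triggered by the primary outcome. A separate analysis plan would have to contradict that text to repair it.

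**Conclusion.** The point holds in conditional form. The exclusion for violation or loss of adherence can depend on antibiotic use, and a treated override after the optional CXR is a concrete route that favours the experimental arm. If it is the only deviation, the exaggeration is about 0.8-1.7 points at f = 0.10 and 1.9-4.0 at f = 0.25, against received reductions of 12.1-25.3 and 9.4-20.5 points. At these rates it would distort the estimate rather than create it.

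These sizes rest on assumed accuracies, independent errors and an unknown f. The sign of the overall bias depends on the mix of deviations in both arms, which the article does not allow anyone to predict. This should be corrected, but the article does not show that the trial's conclusion would be wrong.

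**What to change.** For antibiotic prescription and antibiotic days, state that every randomised child is analysed in the assigned arm, whatever extra imaging was done and whether or not antibiotics followed the algorithm. Restrict the exclusion in the Inclusion and exclusion criteria section to a per-protocol sensitivity analysis for these outcomes.

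Add one table by arm that sets the recommendation from first image plus PCT against antibiotics actually received, counting departures in both directions: treated against the rule, and untreated against a recommendation. The LUS reading, the CXR report and PCT are largely available from the planned procedures.

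The cost is a change of wording and one table, with no extra patients or examinations. The downside is that the observed reduction may be smaller than with exclusion, for example 9.4-20.5 instead of 11.3-24.5 points in the illustration at f = 0.25.

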Quality of care is defined by the World Health Organization as medical care in which the patient is diagnosed and treated correctly, according to current medical knowledge (scientific and technical quality), and to their biological factors (optimal state of health to attain), with a minimum cost (efficiency), minimum possible exposure to risk for more harm, and maximum patient satisfaction [25]. At the hospital level, a quality assurance plan should include different levels of action. The first step is level 1 of quality promotion, which requires institutional support and the availability of clinical and quality protocols. The second step is the research level: descriptive studies for detecting and quantifying a specific situation or health issue, and the use of databases or specific studies to evaluate health services, among others.

Therefore, we propose this clinical trial, based on combining LUS and PCT in an algorithm with the aim to improve quality of care in children with pneumonia in a PICU. We hypothesize that the diagnostic performance of LUS and PCT will be better than conventional CXR.

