### Study aim

Our primary goal is to improve the quality of care in children with suspected community or nosocomial pneumonia in a PICU.

The main objectives are:
To assess whether a diagnostic algorithm for pneumonia that combines LUS and PCT may be useful in indicating and determining the duration of antibiotic treatment.To analyse the sensitivity and specificity of LUS, compared to CXR, for severe community or nosocomial pneumonia.

The secondary aims are:
To quantify the irradiation dose avoided using LUS to replace CXR, and to determine if there is an associated decrease in costs.To analyse interobserver agreement in LUS

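### Both arms follow the same PCT rule, so the trial compares LUS with CXR as first image; the hypothesis misnames the comparator and an unstratified prescribing test loses power

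*Protocol article*

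**What the plan says.** The Background section of the protocol article states the hypothesis: "We hypothesize that the diagnostic performance of LUS and PCT will be better than conventional CXR". The Outcomes section words the success criterion in the same spirit: "The antibiotics protocol guided by LUS and PCT will be considered an improvement in the quality of care", on condition that prescribing and days on antibiotics fall. The Conclusion again credits the PCT and LUS algorithm.

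The Methodology section gives the rules for the LUS arm in three branches:
- "If PCT is < 1 ng/mL and LUS is not suggestive of bacterial pneumonia (normal or viral), the patient will not receive an antibiotic"
- "If LUS is suggestive of bacterial pneumonia, regardless of PCT value, an antibiotic will be recommended"
- "If LUS is not suggestive of bacterial pneumonia, but PCT values are > 1 ng/mL, an antibiotic will be recommended to cover other infectious etiologies"

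The control arm is introduced with "Criteria to start an antibiotic will depend on the current unit protocol". The three branches listed under that sentence are the ones above with CXR in place of LUS and the same cut-off; the third opens "If CXR is not suggestive of bacterial pneumonia, but PCT value is" above 1 ng/mL. The Abstract (Methods/design) writes a single rule for both arms, with LUS/CXR as the image.

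The Sample size section defines its alternative hypothesis as a difference between LUS and CXR, without mention of PCT. The Statistical analysis section compares categorical variables with a chi-square test. Its only multivariable step is a logistic regression on variables picked by their univariate results.

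**The concern.** A comparison of LUS plus PCT with conventional CXR suggests a control arm managed on CXR without PCT guidance. The trial has no such arm. PCT guides the start of antibiotics identically on both sides, so a favourable result would speak for the choice of image and not for PCT or for adding PCT. If the present wording reaches the report, readers may credit the biomarker with an effect the trial never varied.

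There is a second consequence. Where PCT is above the cut-off, both arms receive the same recommendation whatever the image shows. Those patients add no difference by rule to the comparison of prescribing, yet they enter the all-patient chi-square. The effect is diluted and power is lost that a baseline value already in hand could partly recover.

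**Working it through.** **Step 1: the two rules side by side.** From the Methodology section, each arm recommends an antibiotic if its image suggests bacterial pneumonia or PCT is above 1 ng/mL. Cross PCT (low/high) with what each image would show (+ = suggestive of bacterial pneumonia):

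| PCT | LUS | CXR | LUS arm | CXR arm | Differ? |
|---|---|---|---|---|---|
| low | − | − | no | no | no |
| low | − | + | no | yes | **yes** |
| low | + | − | yes | no | **yes** |
| low | + | + | yes | yes | no |
| high | any of 4 | | yes | yes | no |

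The rules disagree in 2 of the 8 combinations, both with low PCT. All 4 high-PCT combinations give the same recommendation.

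**Step 2: the plan's own figure.** The Sample size section gives 63 per arm for community pneumonia (80% power, two-sided 5%, chi-square). The article does not print the two proportions, so 63 cannot be re-derived. Many pairs come close, for example 60% v 35% or 90% v 70%, each 62 per arm. What follows therefore shows the size of the dilution; it does not measure a loss against the planned power.

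**Step 3: dilution.** Let h be the share of patients above the cut-off, and let p be the share with a positive image among low-PCT patients. Prescribing by rule is h + (1 − h)p, so the difference between arms is (1 − h) times the difference in p. Assumed, since the article gives neither: p = 0.70 (CXR) and 0.40 (LUS); h = 0.3, 0.5, 0.7.

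**Step 4: power.** With z = 1.96 and p̄ the mean of p1 and p2,

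power = Φ{ [ |p1 − p2|√n − z√(2p̄(1 − p̄)) ] / √[ p1(1 − p1) + p2(1 − p2) ] }.

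In a Mantel-Haenszel test, a stratum in which everyone is prescribed an antibiotic contributes nothing to the statistic or its variance. Under full adherence the stratified test over all patients therefore has about the power of the low-PCT patients alone, with n = 63(1 − h) per arm.

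Worked case, h = 0.5:
- Unstratified: 0.85 v 0.70, n = 63. Numerator 0.15 × 7.937 − 1.96 × 0.591 = 0.033; denominator 0.581; Φ(0.057) = 52%.
- Stratified: 0.70 v 0.40, n = 31.5. Numerator 0.30 × 5.612 − 1.96 × 0.704 = 0.305; denominator 0.671; Φ(0.454) = 68%.

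| h | CXR v LUS, all patients | Difference | Unstratified | Stratified |
|---|---|---|---|---|
| 0.3 | 0.79 v 0.58 | 21 points | 72% | 82% |
| 0.5 | 0.85 v 0.70 | 15 points | 52% | 68% |
| 0.7 | 0.91 v 0.82 | 9 points | 31% | 46% |

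A simulation of the Mantel-Haenszel test with random stratum sizes agrees with the last column to within about one percentage point.

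**Step 5: other rates.** With 60% v 35% among low-PCT patients, unstratified power for the same three shares is 53%, 36% and 21%; the formula gives 66%, 51% and 33% stratified. With 70% v 30%, unstratified power is 92%, 74% and 47%. The level depends heavily on the assumed rates; the ordering does not.

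**The case against.** The strongest reply is that the control arm is the unit's current protocol, which on its face already includes PCT. Randomising LUS with PCT against existing care is a legitimate comparison of strategies, and sharing a component with usual care does not spoil it. This stands. A reader might infer that the success criterion in the Outcomes section cannot be answered by the randomised contrast, or that any claim for the combined algorithm must be dropped. The article does not support that: only a separate PCT effect, or superiority over CXR used without PCT, lies out of reach.

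It can also be said that the article already states the narrower contrast in the Abstract, in its second main objective and in the Sample size section. That is true, and it shows that the Background hypothesis is the sentence out of line. That sentence speaks of diagnostic performance rather than prescribing, so the table in step 1 does not test it. The misnamed comparator remains.

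On the analysis, the all-patient difference is a valid policy effect, and dilution is not bias. Positive branches are only recommendations, and a CXR may be requested in the LUS arm, so actual prescribing may differ at high PCT too. It is tempting to make the low-PCT stratum the key estimate, but that would sideline those patients; it is a trade-off, not a correction. The LUS procedure section also says LUS can show early lesions that CXR misses, so even the assumed direction (LUS less often positive) is not given. These points limit the figures and the remedy, but do not remove the power advantage of stratifying.

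Finally, the Study aim section says the algorithm "may be useful in indicating and determining the duration of antibiotic treatment", while the Methodology lists only rules for starting. A reader might call this a contradiction. A condensed article may leave the duration rule to the full protocol, so it is not held against the plan.

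**Conclusion.** The point holds in a limited form. That both arms share the PCT rule follows directly from the Methodology and the Abstract and needs no assumption. The Background hypothesis therefore names the wrong comparator, and no between-arm result can be attributed to PCT. The strategy comparison with current unit care survives if so described.

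That recommendations can differ only at low PCT also follows from the text. The size of the power loss does not. Under the illustrative rates, stratifying gains about 10, 16 and 15 percentage points (82 − 72, 68 − 52, 46 − 31) with 30%, 50% and 70% of patients above the cut-off. This assumes full adherence to the rules, 63 per arm (community pneumonia only), and image-positivity rates and PCT shares that the article does not give. A reader might infer that the trial is underpowered against its own plan. That cannot be shown, because the planned proportions are not printed and the stated main variable is the difference between CXR and LUS, not prescribing.

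**What to change.** 1. Reword the hypothesis in the Background, the success statement in Outcomes and the Conclusion so that the comparison reads as LUS versus CXR as first image within the same PCT-guided rule, the CXR arm being the current unit protocol. State that no separate effect of PCT is claimed.
2. Analyse antibiotic prescription in all randomised patients with a Mantel-Haenszel test stratified by baseline PCT category, in place of the plain chi-square. Use the PCT value on which the starting rule is applied. State which stratum takes a value of exactly 1 ng/mL, since the branches address only values below and above it.
3. Report the low-PCT stratum as a supportive result, not as the key estimate.

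The cost is a few sentences and one pre-specified test on a value the rule already requires for each patient. No extra patients or measurements are needed. The claim becomes narrower.
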